### Participants and recruitment

Eligible PLHIV will be men and women aged 30- to 50 years, diagnosed with HIV/AIDS [26], but asymptomatic and free from opportunist infections. Exclusion criteria will be: a) use of cART for less than 3 years; b) regular physical exercise (≥ 3 days/week during 30 min) in the last 6 months; c) current or past diagnosis of hypertension, coronary artery disease, ischemic disease, pulmonary disease, diabetes mellitus, Chagas disease, tuberculosis, or heart failure; d) malnutrition; e) use of antidepressant or antihypertensive medication, and f) smoking habit. Uninfected controls will be screened for items b, c, d, e, and f.

Forty-two PLHIV will be randomized through a random code generator software (www.randomization.com) at a ratio of 1:1 into intervention or control groups. Therefore, the experiment will have three groups: a) PLHIV under training (PLHIV-T; n = 21), which will enroll in the multimodal exercise training during 12 weeks; b) PLHIV controls (PLHIV-C; n = 21), which will remain in clinical care and shall not to change their physical activity behavior; c) Uninfected controls (CONT; n = 21), which shall not change their physical activity behavior. For ethical reasons, the PLHIV-C group will have the possibility to undertake the exercise training intervention once the trial ends. Outcomes in PLHIV-T and PLHIV-C will be assessed before randomization at baseline and after intervention, whereas in CONT only at baseline to provide reference values. The study flowchart is presented in Fig 2.

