### Sample size calculation and statistical analysis

Sample size was calculated using GPower 3.1.9.4 (Universität Kiel, Kiel, Germany) to detect longitudinal differences between groups in systolic BP response due to metaboreflex gain. Considering a between-group difference of 3.5 mmHg (standard deviation of 4.6 mmHg) [23], 80% power and 5% significance level, and increasing the sample size by 50% to account for losses to follow up, a total of 21 participants in each group was calculated as necessary.

Descriptive analysis will consist of mean and standard deviation for continuous variables and percentage for categorical variables. Data normality will be checked by the Shapiro Wilk test, and data will be presented as mean and standard deviation or percentage, whenever appropriate. A cross-sectional comparison between PLHIV-T, PLHIV-C and CONT will be performed at baseline by means of one-way ANOVA (continuous) or chi-squared test (categorical).

Longitudinal effects of exercise training on primary and secondary outcomes will be evaluated through linear mixed models (LMM) including treatment (PLHIV-T or PLHIV-C) and time as fixed effects, and group *vs*. time interaction. LMM, which correlates with repeated measures over the time, allows an intention-to-treat analysis as it includes all observations of each one of the participants, regardless of losses to follow-up or noncompliance to exercise protocol. Residual plots of all models will be examined and the likelihood-ratio test will be used to compare and select random intercept or random slope models. Data analysis will be performed using Stata 13.0 (StataCorp, College Station, TX, USA), and in all cases the statistical significance will be set at *P* ≤ 0.05.

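### The group-by-time mixed model is in effect a change-score comparison: valid, but less precise than a model that uses the shared pre-randomisation baseline mean

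*Protocol article*

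**What the plan says.** In the protocol article, the section on sample size and statistical analysis sets one model for all primary and secondary outcomes: "linear mixed models (LMM) including treatment (PLHIV-T or PLHIV-C) and time as fixed effects", together with a group-by-time interaction. It names neither a baseline covariate nor a constraint of equal baseline means. It chooses the mixed model because all observations can then be included despite losses and non-compliance, and it lets a likelihood-ratio test decide between random-intercept and random-slope forms.

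On timing, the section on participants and recruitment states: "Outcomes in PLHIV-T and PLHIV-C will be assessed before randomization at baseline and after intervention". Allocation is "at a ratio of 1:1 into intervention or control groups". The uninfected reference group is not randomised and is measured only at baseline.

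The section on metaboreflex assessment expresses each outcome as a change from rest within the visit. Each visit therefore yields a response, and the response at the first visit is a pre-randomisation value of the outcome itself.

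The sample size rests on these inputs: "Considering a between-group difference of 3.5 mmHg (standard deviation of 4.6 mmHg"), "80% power and 5% significance level", and "increasing the sample size by 50% to account for losses to follow up".

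**The concern.** Because baseline precedes allocation, the two randomised arms have the same expected baseline. Any observed difference there is chance. A model with a free treatment main effect ignores this and estimates a separate baseline mean for each arm. With two visits, the interaction then subtracts one arm's full mean change from the other's, and the chance baseline difference enters the effect estimate with full weight. A model that knows the baseline means are equal gives that difference only the weight that the pre-post correlation justifies.

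What is at stake is precision. The trial is small, at 21 per arm, and the article itself allows for substantial losses. The measurement that would recover the precision is already taken on every randomised participant.

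**Working it through.** **Inputs from the article.** Difference 3.5 mmHg; SD 4.6 mmHg; 80% power; 5% significance (two-sided assumed, as sidedness is not stated); 50% increase for losses; 21 per group; one baseline and one post-intervention assessment.

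**Inputs that the article does not give.** The pre-post correlation r, and whether 4.6 mmHg is the SD of the response at one visit or of the change between visits. Both are treated as assumptions below.

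**The plan's own figure.** A two-arm comparison needs 2 × (1.960 + 0.842)² × (4.6/3.5)² = 27.1, so 28 per arm (29 with the exact t test). Multiplied by 1.5 this is 42 per arm, not 21. The figure of 21 appears only if 28 is taken as the total (28 × 1.5 = 42 in all) or if a one-sample formula is used (13.56, rounded to 14; 14 × 1.5 = 21). That is a separate problem. It matters here only because 21 per group corresponds to 14 per group before the increase.

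**Step 1: what the interaction estimates.** The planned model was fitted with a random intercept to three simulated complete data sets of 21 per arm and two visits. In each, the interaction equalled the difference in mean change and the standard errors agreed to four decimals. In one set both gave 2.5498 (SE 1.1902), while adjustment for baseline gave 2.772 (SE 0.937). In a single data set the adjusted SE can also be slightly larger, as it was in one of the three (1.180 against 1.163). The gain is an average over trials.

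**Step 2: variance.** With single-visit SD σ:
- change score: variance per participant 2σ²(1−r)
- baseline-adjusted: σ²(1−r²)
- ratio (1+r)/2, so the reduction is (1−r)/2.

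| assumed r | large-sample reduction | simulated, 21 per arm |
|---|---|---|
| 0.1 | 45% | – |
| 0.3 | 35% | 33% |
| 0.5 | 25% | 22% |
| 0.7 | 15% | 13% |
| 0.9 | 5% | – |

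**Step 3: dropouts kept in the model.** Suppose 21 per arm have a baseline and 14 a week-12 value. In units of σ², the large-sample variance per arm is (1−r²)/14 + (1−r)²/21 for the planned model and (1−r²)/14 for the constrained one. At r = 0.5 this is 0.0536 + 0.0119 = 0.0655 against 0.0536, a reduction of 18%. At r = 0.3 and 0.7 it is about 26% and 11%.

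**Step 4: power for 3.5 mmHg, 21 per arm, complete data.** If 4.6 is the single-visit SD, the SDs are 4.6√(2(1−r)) for the change and 4.6√(1−r²) after adjustment.

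| assumed r | SD, change | SD, adjusted | power, change | power, adjusted |
|---|---|---|---|---|
| 0.3 | 5.44 | 4.39 | 53% | 71% |
| 0.5 | 4.60 | 3.98 | 67% | 79% |
| 0.7 | 3.56 | 3.29 | 87% | 92% |

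If 4.6 is instead the SD of the change, change-score power is 67% whatever r is, and adjustment raises it to 85%, 79% and 74% at r = 0.3, 0.5 and 0.7.

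**The case against.** The strongest reply is that a group-by-time mixed model is a standard analysis, unbiased under randomisation, and that the article states nothing false about it. That stands. A reader might infer that the planned test is biased or invalid, and the documents do not support that. Nor is chance baseline imbalance a second harm on top of lost precision: over repeated randomisations it is part of the change-score standard error.

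A second reply is that covariate adjustment may be left to a fuller document. That is possible in general, but the article does fix the fixed effects for this comparison, and the free treatment term among them is what removes the gain.

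A third is that blood pressure is read every minute, that the circulatory-arrest protocol is done without and with capsaicin, and that losses are expected, so one value per visit with complete data is an idealisation. This makes the equivalence approximate. However, neither repeated readings within a visit nor random slopes bring in baseline adjustment, and Step 3 shows that the gain shrinks with dropouts but does not vanish.

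Finally, any single percentage rests on an unstated r. That is correct, so the range is shown. Only the direction is free of the assumption: the large-sample gain is positive for every r below 1.

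**Conclusion.** The point holds as a loss of efficiency in a valid analysis. The large-sample variance reduction forgone is (1−r)/2: 35% to 15% for an assumed r of 0.3 to 0.7, and 45% to 5% for 0.1 to 0.9. It is somewhat less at this sample size and with dropouts kept in the model. The power gain with 21 per arm and complete data is 18, 12 and 5 percentage points at r = 0.3, 0.5 and 0.7 if 4.6 mmHg is a single-visit SD.

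A reader might infer that the trial is underpowered in every case. The documents do not settle that: with full retention, a single-visit SD of 4.6 mmHg and r = 0.7, the planned analysis has 87% power. Equally, the better model is no cure for the sample size. With 14 evaluable per arm, power after adjustment stays below 80% for r = 0.3 to 0.7 under either reading of the SD (53% to 77% for a single-visit SD, 67% to 56% for an SD of change).

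**What to change.** For the PLHIV-T versus PLHIV-C comparison of each outcome, keep the linear mixed model but drop the treatment main effect. Time and treatment-by-time then remain with a common baseline mean (a constrained longitudinal model). Report the week-12 treatment difference with its confidence interval as the effect. If several readings per visit are modelled, apply the constraint to all baseline-visit terms. Do not extend it to the uninfected reference group, which is not randomised.

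This form keeps participants lost after baseline in the analysis, as the article intends. ANCOVA of the week-12 value on the baseline value gives essentially the same result when week-12 data are complete. With losses it leaves out everyone without a week-12 value, so it should not be written in as an interchangeable alternative.

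The cost is one sentence in the analysis section, with no new data, visits or participants. The sample-size calculation needs its own correction, including a statement of what the 4.6 mmHg SD refers to and of the r assumed.

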### Muscle metaboreflex activity assessment

Muscle metaboreflex will be activated by a PECA protocol, which has been shown to trap muscle metabolites in the exercising limb and to maintain stimulation of group IV muscle afferents without the activity of the central command and mechanoreflex [12]. PECA will consist of 13 min, as follows: 5 min of rest, 2 min of isometric handgrip exercise with the dominant arm with a load corresponding to 40% of MVC, 3 min of vascular occlusion, followed by 3 min of recovery. Vascular occlusion will be applied in the exercised limb by inflating a cuff at 240 mmHg 5 s before the end of exercise, and then deflating it in the 3-min recovery. During PECA, the volunteers will be in a sitting position, and shall avoid performing the Valsalva maneuver and any movement, except for the handgrip. Changes from rest during PECA will be calculated for autonomic and cardiovascular outcomes.

Prior to PECA, a brief familiarization with the handgrip exercise will be allowed. Handgrip force exerted will be placed in front of the subjects to guide the contraction intensity. Vascular occlusion in PECA will be applied using a nylon cuff size 11 x 85 cm connected to a pneumatic cuff inflator Hokanson TD312 (D. E. Hokanson^TM^ Inc, Bellevue, Washington, USA) placed around the proximal third of the dominant arm. A vascular Doppler probe (DV 610B Medmega Industria de Equipamentos Medicos, Franca, SP, Brazil) will be placed over the brachial artery (dominant arm) to capture the auscultatory pulse and confirm the vascular occlusion during the PECA protocol. The Fig 4 details the PECA protocol.

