### Primary outcomes

#### Blood pressure

Systolic and diastolic BP will be assessed in the non-dominant arm using a digital sphygmomanometer (Omron HEM—7113, Kyoto, Japan) positioned around the proximal third of the non-dominant arm. Data will be assessed at rest, and every minute during mental stress and muscle metaboreflex assessments.

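### With only two visits, a likelihood-ratio choice between random intercept and random slope is uninformative on one value per visit, and mildly anti-conservative if per-minute readings are modelled

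*Protocol article*

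**What the plan says.** In the protocol article, the section on sample size and statistical analysis evaluates the effect of training on every primary and secondary outcome by linear mixed models "including treatment (PLHIV-T or PLHIV-C) and time as fixed effects, and group *vs*. time interaction". The random part is not fixed in advance: "the likelihood-ratio test will be used to compare and select random intercept or random slope models". The same section says of the model that "it includes all observations of each one of the participants".

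The section on participants and recruitment sets the schedule: "Outcomes in PLHIV-T and PLHIV-C will be assessed before randomization at baseline and after intervention". That is two visits per randomised participant.

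Within a visit, blood pressure is read repeatedly. The blood pressure section says: "Data will be assessed at rest, and every minute during mental stress and muscle metaboreflex assessments". The metaboreflex test includes "2 min of isometric handgrip exercise with the dominant arm with a load corresponding to 40% of MVC, 3 min of vascular occlusion", and "Changes from rest during PECA will be calculated for autonomic and cardiovascular outcomes". The article does not say whether such a change is one summary per visit or one value per minute, nor whether time in the model means visit or minute.

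**The concern.** A random slope describes how participants differ in their trend over time. Two visits with one value each cannot separate such differences from residual error, so the test would compare a usable model with one that cannot be estimated in full, or that describes something else.

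If the per-minute readings are the observations, the random-slope model can be estimated, but the selection rule brings a different risk. A random intercept correlates all readings of a participant equally, so two readings from one visit are modelled as no more alike than two readings from different visits. Any real day-to-day shift of a participant is then missing from the error of the group-by-time effect, which is the effect the trial is designed to test. A non-significant likelihood-ratio test in 42 people is weak evidence that no such shift exists. The structure chosen could also differ from one outcome to the next.

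**Working it through.** **Inputs.** From the article: two visits; 21 per arm; a 50% allowance for losses, so 21/1.5 = 14 completers per arm is a size the plan allows for; 3 minutes of occlusion, or 5 minutes of handgrip plus occlusion, so m = 3 or 5 readings per visit. The article gives no variance components, so these are assumed: between-participant variance 2, reading (residual) variance e = 1, and participant-by-visit variance v from 0 to 2 times e. There is no figure of the plan's own to reproduce on this point.

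**Step 1: one value per visit, correlated effects.** Code time 0 and 1, with intercept variance a, slope variance b, their covariance c and residual s:

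- V(baseline) = a + s
- V(week 12) = a + b + 2c + s
- Cov = a + c

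There are four unknowns and three equations (rank 3), so no unique solution exists. In one simulated two-visit data set (n = 42), four optimisers reached the same log-likelihood (-240.014) with residual variances from 5.9 to 7.4.

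**Step 2: one value per visit, uncorrelated effects.** With c = 0 the model is identified, and b = V(week 12) - V(baseline), bounded at 0. The test therefore asks only whether variance rose. In simulation it kept the random intercept in 96-99% of runs.

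**Step 3: effect on the treatment comparison.** The group-by-time standard error depends on the variance of a participant's change, V(baseline) + V(week 12) - 2Cov. This is 2s under random intercept and b + 2s under the uncorrelated slope model. With complete data both are fitted to the same observed quantity. The relative difference was below 0.0001, and type I error was 5.8% under both.

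**Step 4: per-minute readings, time = visit, random intercept always used.** The true variance of a participant's change in visit means is 2(v + e/m). The random-intercept model pools one between-visit degree of freedom (expected mean square e + mv) with 2(m - 1) within-visit degrees of freedom (expected mean square e). In large samples it therefore uses 2(e/m + v/(2m - 1)).

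For m = 3 and v/e = 0.25: true/modelled = (0.25 + 0.333)/(0.333 + 0.05) = 0.583/0.383 = 1.52. The standard error is too small by a factor of √1.52 = 1.23. The nominal 1.96 becomes 1.96/1.23 = 1.59, a two-sided error of about 11%. Simulation with 21 per arm gave 12%.

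**Step 5: the planned procedure, with selection.** Null data were simulated (1,500 runs per setting), with maximum likelihood fits, a likelihood-ratio test at 0.05 and then a Wald z test of group by time. For m = 3:

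| v/e | random intercept kept, 21 per arm | kept, 14 per arm | type I error, random intercept always, 21 per arm |
|---|---|---|---|
| 0.1 | 87% | 91% | 7% |
| 0.25 | 51% | 65% | 12% |
| 0.5 | 11% | 28% | 16% |

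Type I error of the whole procedure, over 3 or 5 readings and 21 or 14 per arm:

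- no visit-level variance: 4.3-5.7%
- v/e from 0.1 to 2: 5.2-9.9%
- peak of 8.6-9.9%: at v/e = 0.25 with 3 readings, 0.1 with 5 readings, or up to 0.5 with 14 per arm
- t-test on each participant's change in visit means: 3.8-6.3% throughout

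At v/e of 1 or more the test keeps the random intercept in 3% of runs or fewer, which is why the error does not go on rising.

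**Step 6: how much is due to selection.** At 14 per arm, m = 3 and v/e = 0.25, the errors were 12.1% with random intercept always, 9.1% after selection against the correlated slope model, 6.5% with that slope model always, and 4.8% with the t-test. So 9.1 - 6.5 = 2.6 percentage points come from selection. Much of the remaining 6.5 - 4.8 = 1.7 points reflects the z reference in a small sample.

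**The case against.** The strongest reply is that with one value per visit the step is harmless. A reader might infer from the non-identification that the P value for group by time has no unique value. It does not follow: what is undetermined is how the covariance splits into components, and Step 3 shows the standard error unchanged with complete data. In a separate simulation with one third lost at week 12, random intercept and the selected model both gave about 7-8%, so selection made no difference there either. The article also does not say that the random effects are correlated. All of this stands. It makes the step pointless on this reading, but not harmful.

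The second reply is that the per-minute reading is not in the text. The blood pressure section describes collection, changes from rest are to be calculated, and the sentence on including all observations goes on to losses and non-compliance, so it may concern retention only. Outcomes such as maximal grip strength have one value per visit anyway. This also stands: the inflation is conditional. How a phase is summarised may be left to a fuller document, but the selection rule is stated in the article, and no statement there excludes the reading under which it does harm.

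Two further inferences should be resisted. A random-intercept model does not treat readings as independent; it treats them as independent given the participant. And error rates of 7-41% belong to a random intercept used regardless of the test, which is not what the plan describes.

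**Conclusion.** The stated selection rule does not suit a two-visit design. On one value per visit it is not identified or tests only a rise in variance, with no effect on the group-by-time inference when data are complete. On per-minute readings with time as visit, it raises type I error from about 5% to about 6-10% when visit-level variance is small to moderate. The size rests on assumed variance components, on a Wald z test, and on minutes being the unit of analysis, which the article neither states nor excludes. If time means minute, neither candidate has a visit-level term and the test offers no protection; a random slope on minute was not simulated. The documents do not support saying that the primary P value will be wrong. They do support replacing the step.

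**What to change.** Delete the likelihood-ratio selection. State that each phase is reduced to one value per participant, visit and condition, for example the mean over the phase. Then name one model, fitted by REML with small-sample degrees of freedom. Either of these would serve:

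- **Baseline-adjusted:** ANCOVA, or an unstructured 2x2 visit covariance with the baseline means of the two randomised arms constrained equal.
- **The planned group-by-time model** with an unstructured 2x2 covariance. With complete data this is equivalent to comparing change scores, not to ANCOVA, so the choice between the two should be explicit.

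If per-minute values are to be kept, prespecify a random participant-by-visit effect, define time as visit or minute, and still drop the test. The cost is analysis wording; measurements, schedule and sample size do not change.

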### Potential harms

In the event of any clinical intercurrence during the training sessions or experimental protocol, the participants will be referred to the University Hospital for medical care. Any adverse clinical event will be reported to the ethics committee.

### Data management, accessibility, and dissemination policy

A trained research assistant will be responsible for including all primary and secondary outcomes in an Excel spreadsheet in the proper format for analysis, which will be checked by the principal investigator. Unnamed data collected and research results will be deposited in the cloud (Dropbox) and may be consulted after permission granted by the principal investigator. All personal data will be properly stored in folders that will be kept confidential, and will not be passed on to any third party without prior consent from the participants. At the study end, each participant will receive a full report with the results of their assessments. The results of the study will be publicized in scientific congresses and journals.

